## Abstract

**Background:**

The effects of velocity-based resistance training (VBRT) in institutionalized older adults remain poorly explored. This protocol aims to describe a study designed to i) analyze the effects of a 9-month VBRT program on skeletal muscle size, muscle function, physical performance, disability, cognitive function and frailty in nursing home residents, ii) compare the impact of different velocity loss (VL) thresholds (10% vs. 20%), and iii) determine the residual effect of the intervention after 6 months exercise cessation.

**Methods:**

Nursing home residents aged ≥65 years will participate in this experimental study. Participants will complete a 4-week control period followed by a 9-month VBRT program and 6 months of follow-up after exercise cessation. The intervention will consist of VBRT twice a week using the leg press exercise for 9 months. The participants will be randomly assigned to two VL groups: 10% vs. 20% VL, performing *n* repetitions at 60% of estimated maximal isometric force until reaching their prescribed VL. To minimize training volume differences, the 10% VL group will complete 4 sets, while the 20% VL group will complete 3 sets. Outcomes will include muscle size of rectus femoris and vastus lateralis (ultrasound), muscle function (sit-to-stand muscle power and force-velocity relationship parameters), physical performance (Short Physical Performance Battery and walking tests), disability (Barthel and Lawton Indexes), cognitive function (Mini-Mental State Examination) and frailty (Fried Phenotype and Frailty Trait Scale). The time course of the exercise-induced adaptations will be assessed throughout the study.

**Discussion:**

We hypothesize that VBRT will exhibit meaningful benefits in muscle size, muscle function, physical performance, disability, cognitive function and frailty among institutionalized older adults, with no significant differences between 10% and 20% VL thresholds. While deconditioning is predictable after 6 months of exercise cessation, the investigated outcomes are expected to remain significantly and positively elevated compared to baseline values. This study will help to identify innovative actions to improve overall health and endorse exercise practice in older adults living in nursing homes.

**Trial Registration:**

ClinicalTrials.gov, identifier NCT07027397.

## Introduction

1

Aging is inevitably accompanied by a physiological decline in endocrine, mitochondrial, neural and muscle functions (Cruz-Jentoft et al., 2010; Clark, 2019; Ara et al., 2025). These age-related alterations in conjunction with physical inactivity lead to physical dysfunction, cognitive impairment and disability in activities of daily living (ADL). All these negative consequences of aging can ultimately lead to nursing home admission (Luppa et al., 2010). Evidence suggests that institutionalized older adults constitute a vulnerable population characterized by relatively high prevalence rates of frailty and cognitive impairment (Kojima, 2015; Chen et al., 2023). These clinical conditions combined with an expected 2.2-fold increase in institutionalized older people in the next decades (Pickard et al., 2007) pose a major public health challenge. In this regard, cost-effective strategies are needed in long-term care facilities to reduce the high economic costs related to healthcare in institutionalized older adults (Tang et al., 2022).

The implementation of physical exercise programs is one of the most effective interventions for improving health and wellbeing of institutionalized adults (Valenzuela et al., 2023; Xu et al., 2023; Izquierdo et al., 2025). In particular, resistance training (RT) is widely recognized as a cornerstone intervention to mitigate, and even counteract, age-related declines in muscle mass and neuromuscular function, thereby reducing the risk of sarcopenia, frailty and disability in older adults (Fragala et al., 2019). In addition to neuromuscular adaptations, RT exerts positive effects on cognitive function (Cadore et al., 2014b; Zhu et al., 2025), mitigating age-related cognitive decline in memory, attention, and executive function of older adults.

Technological advances have provided the implementation of device-assisted approaches in RT to facilitate its monitoring and prescription, providing more tailored and potentially more effective RT interventions in younger populations (Courel-Ibáñez et al., 2019; Pérez-Castilla et al., 2019). In this regard, velocity-based resistance training (VBRT), which consist in monitoring repetition velocity and prescribing RT accordingly, is well established in healthy and athletic populations (Pareja-Blanco et al., 2020) and its use is expanding in individuals with pathologies and physical dysfunction (Jimeno-Almazán et al., 2023). VBRT not only helps to objectively determine RT intensity due to the strong relationship between concentric movement velocity and relative intensity (González-Badillo and Sánchez-Medina, 2010; Hernández-Belmonte et al., 2023a), but also RT repetition volume can be prescribed in order to achieve a desirable level of fatigue using velocity loss (VL) thresholds (Sánchez-Medina and González-Badillo, 2011). Despite the benefits of VBRT for exercise monitoring and dosing, its implementation in RT interventions in older adults is poorly explored, specifically using different VL thresholds. In this regard, previous studies with older adults recruited from community-dwelling centers have performed VBRT with 10% (Marques et al., 2022) and 20% VL (Marques et al., 2020); and only one previous study implementing a 10-week VBRT intervention with different VL thresholds has been conducted in older adults from residential care facilities or day centers (Marques et al., 2024). Although some studies have monitored velocity and VL in older adults, none have applied VBRT thresholds exclusively in institutionalized older adults, especially with different VL thresholds. Indeed, exploring different VL thresholds in this population could provide information on which stimulus is most efficient for inducing adaptations while minimizing systemic fatigue.

While traditional RT investigations in older people maximize physiological adaptations through continuous, rigid periodicity and control over short periods of time (e.g., 10 weeks), pragmatic interventions (i.e., adapted to the individuals’ routines and calendar) but longer in time (e.g., >6 months) are needed to elucidate the real-world effectiveness of exercise interventions during aging. Moreover, understanding whether VBRT can induce residual beneficial effects after exercise program cessation (Buendía-Romero et al., 2025) is crucial for designing cost-effective exercise programs in nursing homes with long-term benefits.

Against this background, the present protocol aims to describe a study designed to i) analyze the effects of one season (from Autumn to Summer; 9 months) of VBRT on skeletal muscle size, muscle function, physical performance, disability, cognitive function and frailty in older adults living in nursing homes (primary objective); ii) compare the impact of different VL thresholds (10% vs. 20% VL) (secondary objective I); and iii) determine the residual effect of the VBRT program after 6 months of exercise cessation (secondary objective II).

## Materials and methods

2

### Design and participants

2.1

This study protocol was registered in ClinicalTrials.gov (ID: NCT07027397) and approved by the Clinical Research Ethics Committee of the Toledo Hospital Complex (ID: 710P). The present protocol will be conducted in accordance with the SPIRIT (Standard Protocol Items: Recommendations for Interventional Trials) statement (Chan et al., 2013; Supplementary Table S1). Adults aged ≥65 years living in two nursing homes (Toledo, Spain) will participate in this research. Participants will be informed about the characteristics of the study and will provide their signed consent. The study will include a 4-week control period, followed by 9 months of VBRT in the leg press exercise and a 6-month follow-up in which no exercise intervention will be conducted. All participants will be allocated into the intervention group due to ethical reasons (Izquierdo et al., 2025), and thus the control period will serve as the comparator condition. Participants will be randomized in two experimental groups: 10%VL group or 20%VL group. A randomization sequence stratified by theoretical maximal isometric force (F_0_) and sex will be used to assign participants to both groups.

Following our intentionally pragmatic and translational perspective to investigate the effects of VBRT on skeletal muscle size, muscle function, physical performance, disability, cognitive function, and frailty, the exercise intervention will be conducted over a whole season, including periods in which the intervention will be paused (e.g., Christmas, Easter, summer holidays) and then restarted. Thus, the main outcomes will be assessed at six specific time points as detailed in Figure 1: prior to a 4-week control period (Pre-control), at baseline (T0), post 6 weeks (T1), post 12 weeks (T2), post 23 weeks (T3), and post 39 weeks (T4). Upon completion of the VBRT, a final follow-up will be conducted after 6 months of usual care (T5).

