**FIGURE 1 F1:**

Experimental design overview. The study comprises three phases: a 4-week control period, a 9-month velocity-based resistance training (VBRT) intervention and a 6-month follow-up period. Assessment time points are indicated at specific weeks (w): T0 indicates baseline; T1-T4, intervention assessments; and T5, final follow-up.

The required sample size was determined on the basis of muscle function, using the 5-rep sit-to-stand (STS) muscle power test (Alcazar et al., 2018). According to previous research conducting exercise interventions in nursing home residents (Gutiérrez-Reguero et al., 2024), a within-group difference of +0.64 W·kg^−1^ (95%CI: +0.39 to +0.89) in relative muscle power was expected. Using this effect size (ES = 0.91), a required sample size of 15 participants was calculated in the G*Power software, assuming α = 0.05 and power = 90%. Assuming a maximum loss to follow-up of ∼35%, we will recruit 27 nursing home residents aged ≥65 years to address our primary objective. Exclusion criteria will include: i) uncontrolled hypertension, unstable or exercise-induced angina pectoris or myocardial ischemia or any other medical condition incompatible with physical exercise, ii) bedridden or unable to walk with assistance, and iii) terminal illness. The study will be performed in accordance with the Helsinki Declaration.

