### Statistical analysis

2.5

Data will be presented as mean and standard deviation or 95% confidence interval unless otherwise stated. Normality of distribution will be assessed by the Shapiro–Wilk test. To analyze the effect of VBRT on all outcomes in the whole sample (primary objective), linear mixed-effect models (LMM) will be fitted using Restricted Maximum Likelihood (REML) estimation. The model will include time as a fixed effect and participant ID as a random effect. The control period will be included in the LMM as an additional time level. This will allow for the comparison of change during the non-exercise period against the time-adjusted changes observed during the VBRT intervention. For the secondary analysis, between-group differences after the VBRT (secondary objective I) will be assessed using the same LMM framework and including time and group (10% vs. 20 VL) as fixed effects, and participant ID as a random effect. The residual effects derived from the VBRT program after 6 months of follow-up will be analyzed similarly, with time as a fixed effect and participant ID as a random effect. To preserve Intention-to-Treat (ITT) principles, training adherence will not be included in the primary model. A secondary per-protocol sensitivity analysis using LMM with REML estimation will be conducted across all objectives, including only participants who completed ≥80% of the exercise sessions. Pairwise comparisons will be adjusted using the Bonferroni method. Cohen’s *d* effect sizes will be calculated using the pooled baseline standard deviation and interpreted as: trivial (<0.20), small (0.20–0.49), moderate (0.50–0.79), and large (>0.80). Statistical analyses will be conducted using SPSS (version 26.0, SPSS Inc., United States), and the level of significance will be set at α = 0.05.

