
Regarding the comparison of different VL thresholds in our VBRT program (secondary objective), both intra-set fatigues (i.e., 10% and 20%VL) have been proven effective in improving physical performance and muscle strength in older adults from residential care facilities or day centers (Marques et al., 2024). This is the only study to compare different VL exclusively among institutionalized older adults. In line with the expected findings, we anticipate no significant differences between the 10%VL and 20%VL groups in physical and muscle function, frailty and disability over the experimental period. Given that this between-group comparison is a secondary objective and the study is not formally powered to detect differences between VL thresholds, this analysis should be interpreted as exploratory and hypothesis-generating, with the resulting effect sizes serving to inform sample size calculations for future adequately powered trials. Although higher VL thresholds (i.e., 40%VL) are associated with greater hypertrophy in young populations (Pareja-Blanco et al., 2020), lower VL thresholds (i.e., 10–20%VL) may generate less fatigue and be sufficient to elicit structural adaptations in older adults living in nursing homes, characterized by low muscle mass (Kimyagarov et al., 2012), with comparable results between groups. If these hypotheses are confirmed, VBRT with 10% VL would be an effective and efficient approach for improving health parameters while imposing lower fatigue (Marques et al., 2022).

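### Randomisation is stratified by F0 and sex, but the between-group model omits both: a group main effect or T4 comparison becomes conservative and imprecise, a change-from-T0 comparison does not

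*Protocol article*

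**What the plan says.** Section 2.1 (Design and participants) sets up two arms: "Participants will be randomized in two experimental groups: 10%VL group or 20%VL group". It then fixes the allocation method: "A randomization sequence stratified by theoretical maximal isometric force" (F0) and by sex. The F0 cut-points and the allocation ratio are not given.

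Section 2.5 (Statistical analysis) states that "between-group differences after the VBRT (secondary objective I) will be assessed using the same LMM framework", "including time and group (10% vs. 20 VL) as fixed effects, and participant ID as a random effect". Neither F0 nor sex appears there or elsewhere in the analysis section. No group-by-time term is written, and the text does not fix whether the difference after training is a level at T4 or a change from T0. Pre-control and T0 are both outcome visits in this framework.

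Section 3 (Discussion) limits the weight of the comparison: "the study is not formally powered to detect differences between VL thresholds, this analysis should be interpreted as exploratory and hypothesis-generating". The same paragraph expects no significant difference between arms and wants the effect sizes to help size later trials.

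**The concern.** Stratified allocation balances the arms on F0 and sex, so chance imbalance on these factors contributes less to the estimated group difference. A model without the factors still counts their variation between people as unexplained noise. Its SE for a between-person comparison is then larger than the real sampling variation: intervals are too wide and the test rejects too rarely.

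For some outcomes the link with F0 is built in. F0 is itself an outcome in Table 1, and section 2.2.3 takes the slope and maximal power from the same linear fit. The direction of the error also matters: the hypothesis is that the arms do not differ, and an over-wide interval makes a non-significant result easier to obtain. With 27 participants, precision that costs nothing to recover should be kept.

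**Working it through.** **The plan's own figure.** The only sample-size figure is for the whole-sample objective: "Using this effect size (ES = 0.91), a required sample size of 15 participants was calculated in the G*Power software". A two-sided paired t-test with d = 0.91 and α = 0.05 gives n = 15 with power 0.906, so it reproduces. The article gives no SE, power or sample size for the between-group comparison.

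**Inputs.** From the article: 27 participants; six main assessments (Pre-control, T0 to T4); the strata and model terms above. Assumed, because the article does not give them: near-equal arms; an F0 split at the median; a random-intercept structure with complete data; ICC 0.6 to 0.9; and R², the share of between-person variance explained by F0 and sex, 0.1 to 0.5. Total variance at one visit is set to 1, so SEs are in SD units.

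**Step 1: ratio of unadjusted to adjusted SE.**
- Level at T4: 1/√(1 − ICC·R²). ICC 0.6, R² 0.1: 1/√0.94 = 1.031. ICC 0.9, R² 0.5: 1/√0.55 = 1.348.
- Group main effect over six visits: √(V/(V − ICC·R²)), with V = ICC + (1 − ICC)/6. ICC 0.6, R² 0.1: √(0.667/0.607) = 1.048. ICC 0.9, R² 0.5: √(0.917/0.467) = 1.402.
- Change from T0: the participant's intercept, and with it any stable F0 or sex effect, drops out of the difference. Ratio 1.

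**Step 2: calibration.** Simulated stratified-block allocation, N = 27, ICC 0.8, 4,000 runs per setting:

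| Contrast | R² | Model SE, unadjusted | Actual SE, unadjusted | Type I, unadjusted | Model SE, adjusted | Type I, adjusted |
|---|---|---|---|---|---|---|
| Main effect | 0.1 | 0.353 | 0.340 | 0.044 | 0.338 | 0.051 |
| Main effect | 0.3 | 0.354 | 0.317 | 0.029 | 0.300 | 0.050 |
| Main effect | 0.5 | 0.356 | 0.290 | 0.018 | 0.257 | 0.056 |
| T4 level | 0.1 | 0.386 | 0.374 | 0.046 | 0.373 | 0.051 |
| T4 level | 0.3 | 0.387 | 0.351 | 0.030 | 0.339 | 0.048 |
| T4 level | 0.5 | 0.390 | 0.333 | 0.021 | 0.303 | 0.053 |
| Change from T0 | 0.3 | 0.243 | 0.246 | 0.053 | 0.246 | 0.054 |

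The Monte Carlo SE of a 5% rate is √(0.05·0.95/4000) = 0.003. At R² 0.3 the mean interval half-width falls from 0.723 to 0.614 (main effect) and from 0.790 to 0.694 (T4).

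**Step 3: REML mixed models** (N = 27, ICC 0.8, R² 0.3, 60 runs), mean SE without and with F0 and sex: main effect 0.352 and 0.296; T4 difference 0.386 and 0.335; change from T0 0.241 and 0.241.

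**Step 4: own pre-training values.** With correlation r between visits, the variance of change from T0 is 2(1 − r). The residual variance at T4 given the mean of Pre-control and T0 is 1 − 2r²/(1 + r).
- r = 0.6: 0.550 against 0.800; √(0.550/0.800) = 0.829, SE 17% smaller.
- r = 0.9: 0.147 against 0.200; √(0.147/0.200) = 0.858, SE 14% smaller.

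**The case against.** The strongest reply is that this design invites a comparison of change: visits are repeated, Pre-control and T0 are time levels, and the question is about training adaptation. For that contrast nothing is too wide and nothing is miscalibrated, as steps 1 to 3 show. This stands in full. A reader might infer that every between-group interval in this trial is inflated; the documents do not support that, because section 2.5 leaves the contrast open. Equally, the model as literally written has only a group main effect, which averages in the pre-training visits, and adding F0 and sex alone would not turn it into a post-training difference.

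The second reply is that the prognostic strength of F0 and sex is unknown. This also stands. At R² 0.1 the unadjusted SE is only about 3 to 5% larger and type I error is close to nominal. A reader might infer a type I error of 0.5 to 2% by simulating 18 completers with one measurement each and one perfectly balanced stratifier at R² 0.3 to 0.5. That is an upper-end case and not the planned model, which uses repeated visits and follows intention-to-treat principles.

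Third, the harm is limited. Omitting balanced covariates does not bias a linear estimate, the error is conservative, and Cohen's d is scaled by the pooled baseline SD and not by the model SE. The point effect sizes therefore do not depend on that SE, although the intervals for the group difference do.

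Fourth, once own pre-training values are used, the stratifiers add little. With A = ICC(1 − R²) and W = 1 − ICC, the residual variance is A + W − A²/(A + W/2). At ICC 0.8 it is 0.289 without the stratifiers and 0.285 with them at R² 0.3 (0.760 − 0.314/0.660), under 1% in SE. At ICC 0.6 and R² 0.5 it is 0.550 against 0.520, about 3%. The pre-training values then carry most of the gain.

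That the article is condensed does not answer the point: it lists the model's terms and even explains why adherence is left out of the primary model.

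**Conclusion.** The point holds conditionally. For the group main effect as written, or a difference in level at T4, omitting the stratification factors gives an SE about 5 to 40% or 3 to 35% larger than the adjusted one (ICC 0.6 to 0.9, R² 0.1 to 0.5). Type I error is about 0.02 to 0.046 at ICC 0.8. Part of this is miscalibration and part is precision forgone: for the main effect at R² 0.3 the reported SE of 0.354 compares with an actual 0.317, and adjustment brings it to 0.300. For change from T0 the loss from omitting the stratifiers is essentially nil, and the available gain is the 14 to 17% from own pre-training values, assuming a visit correlation of 0.6 to 0.9. All these figures rest on assumed ICC and R², a random-intercept structure and complete data.

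A reader might also infer that the primary result is compromised. It is not: the primary analysis is a whole-sample comparison over time with no group term. The finding concerns secondary objective I only. It is not fatal, but it should be corrected before analysis because the remedy is cheap and helps under either reading.

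**What to change.** In the between-group models for secondary objective I:

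1. Add sex and baseline F0 (continuous) as fixed effects. Where F0 is the outcome, its own baseline serves as this term.
2. Use the pre-training values in one of two ways: take the mean of Pre-control and T0 as a covariate and remove those visits from the outcome vector, or keep them as outcomes and constrain the arms to equal pre-training means.
3. Include a group-by-time term and name the group difference at T4 as the contrast for the post-training comparison.

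Cost: about three degrees of freedom, which is not negligible with 27 participants, and a modest restructuring of the model. No new data are needed, since all these values are collected before training starts. The whole-sample primary model needs no change.

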**FIGURE 1 F1:**

Experimental design overview. The study comprises three phases: a 4-week control period, a 9-month velocity-based resistance training (VBRT) intervention and a 6-month follow-up period. Assessment time points are indicated at specific weeks (w): T0 indicates baseline; T1-T4, intervention assessments; and T5, final follow-up.

The required sample size was determined on the basis of muscle function, using the 5-rep sit-to-stand (STS) muscle power test (Alcazar et al., 2018). According to previous research conducting exercise interventions in nursing home residents (Gutiérrez-Reguero et al., 2024), a within-group difference of +0.64 W·kg^−1^ (95%CI: +0.39 to +0.89) in relative muscle power was expected. Using this effect size (ES = 0.91), a required sample size of 15 participants was calculated in the G*Power software, assuming α = 0.05 and power = 90%. Assuming a maximum loss to follow-up of ∼35%, we will recruit 27 nursing home residents aged ≥65 years to address our primary objective. Exclusion criteria will include: i) uncontrolled hypertension, unstable or exercise-induced angina pectoris or myocardial ischemia or any other medical condition incompatible with physical exercise, ii) bedridden or unable to walk with assistance, and iii) terminal illness. The study will be performed in accordance with the Helsinki Declaration.

